Symptoms thought to be associated with COVID-19, including but not limited to: fever, cough, fatigue, dyspnoea, sputum production, anosmia, change in sense of taste, shortness of breath, myalgia, chills, dizziness, headache, sore throat, hoarseness, nausea, vomiting, diarrhoea, nasal congestionAcute respiratory distress syndromeEither clinical or radiological evidence of pneumoniaAtypical presentations, for example an acute functional decline or frailty syndrome in an older person, if they are immunocompromisedSymptoms and lived or worked in close contact with somebody who has tested positive for SARS-CoV-2, including NHS staff

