### Composite reference standards

An assumption of standard diagnostic accuracy studies is that the reference standard is infallible. This constrains the performance of the index test to the performance of the reference standard and assumes every time the tests get different results the reference is correct and the index is incorrect. There is evidence of substantial heterogeneity of diagnostic accuracy of SARS-CoV-2 d/rRT-PCR testing, with reported false negative rates of 18–58% [36]. Both clinical context and repeated testing are highly relevant to calculating the likelihood of true negative cases [37], and so we will undertake further analyses using the composite reference standard.

Composite reference standard 1 will be designed to minimise false negatives (FNs), and composite reference standard 2 will be designed minimise false positives (FPs). Both composite reference standards will be constructed considering paired antibody test results, patient reported outcomes, linked EHRs for outcomes related to COVID-19, such as hospitalisation or death, other test results (Table 4).

**Table 4 Tab4:** Potential use of tests to enhance the reference standard. Information in the table refers to hypothetical combinations of results in which the enhanced reference standard result would be considered different from the original reference standard result. A cell-by-cell interpretation of each scenario follows.

	Minimise FN for current infection		Minimise FN for past infection	
Visit (day)	1 (0)	2 (28)	1 (0)	2 (28)
**SARS-CoV-2 RT-PCR**	Negative (FN)	N/A	Negative	N/A
**COVID IgG**	Negative	Positive	Negative (FN)	Positive
Or:	Subsequent positive SARS-Cov-2 RT-PCR result (within 28 days)		-	
Or:	Hospital admission or death (within 28 days) citing SARS-CoV-2 as probable cause		Hospital admission or death (within 28 days) citing SARS-CoV-2 as probable cause	
	**Minimise FP for current infection**		**Minimise FP for past infection**	
**Visit (day)**	1 (day 0)	2 (28)	1 (day 0)	2 (28)
**SARS-CoV-2 RT-PCR**	Positive (FP)	N/A	Negative	N/A
1.1.35. **COVID IgG**	Negative	Negative	Positive (FP)	Negative
And:	No subsequent positive SARS-Cov-2 RT-PCR result (within 28 days)		-	
And:	No hospital admission or death (within 28 days) citing SARS-CoV-2 as probable cause		No hospital admission or death (within 28 days) citing SARS-CoV-2 as probable cause	

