Minimise FN (false negative) for current infection: If the COVID-19 RT-PCR reference test gives a negative result, it can be considered a false negative if the IgG result is positive at 28 days (newly positive or titres have increased), OR if a subsequent SARS-Cov-2 RT-PCR result (within 28 days) was observed, OR if there was a hospital admission or death (within 28 days) citing SARS-CoV-2 as probable cause

Minimise FP (false positive) for current infection: If the COVID-19 RT-PCR reference test gives a positive result, it can be considered a false positive if the IgG result is negative at both baseline and 28 days, AND if no subsequent SARS-Cov-2 RT-PCR result (within 28 days) was observed, AND if there was no hospital admission or death (within 28 days) citing SARS-CoV-2 as probable cause

Minimise FN (false negative) for past infection: If the baseline reference IgG test result is negative, it can be considered a false negative if the 28-day IgG test result is positive, OR if there was a hospital admission or death (within 28 days) citing SARS-CoV-2 as probable cause

Minimise FP (false positive) for past infection: If the baseline reference IgG test result is positive, it can be considered a false positive if all other tests at baseline and at 28 days are negative, AND there has been no hospital admission or death (within 28 days) citing SARS-CoV-2 as probable cause

Paired antibody testing at 0 and 4 weeks will identify changes in antibody levels over time. These serial laboratory samples will allow us to identify antibody changes to discriminate between current and past infection, and to highlight possible FP and FN RT-PCRs, whilst it remains possible that infection could occur after the index test but prior to the day 28 serology sample, this is unlikely to be a frequent event.

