### Summary statistics of diagnostic accuracy

Sensitivity, specificity, and positive and negative predictive values for each POCT will be calculated with exact 95% confidence intervals.

For the primary outcome and first secondary outcome:

For consecutive POCTs for active infection, the diagnostic accuracy of each POCT will be summarised independently using 2 × 2 tables for POCT (+/-) and the current standard PHE reference test (+/-) for active infection. For consecutive POCTs for past infection, the diagnostic accuracy of each POCT will be summarised independently using 2 × 2 tables for POCT (+/-) and the current standard PHE reference test (+/-) for past infection. Measures of diagnostic accuracy will also be presented adjusted for imperfect reference standard bias, using the best available estimate of the accuracy of the PHE reference test.

For the second and third secondary outcomes:

For consecutive POCTs for active infection, the enhanced diagnostic accuracy of each POCT will be summarised independently using 2 × 2 tables for POCT (+/-) and the composite reference standards as outlined in Table 4 (+/-). For consecutive POCTs for past infection, the enhanced diagnostic accuracy of each POCT will be summarised independently using 2 × 2 tables for POCT (+/-) and the composite reference standards (+/-) for past infection.

Results for the primary outcome will be stratified by adults vs children, by age group (< 16, 16–40, 40–60, 60+ years), by gender, by ethnicity and by spectrum of disease (a combined measure of symptom severity and duration). A further subgroup analysis will test for differences in diagnostic performance by practice, and if any differences are detected, associations with practice size, location and model of care will be explored.

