### Stopping criteria

Assuming a test with 90% sensitivity, a 99% specificity, and a pre-test probability (prevalence) of 30%, we would require 200 participants to meet the minimum thresholds as stated above. This would also mean that tests with more than seven false negatives or two false positives could be immediately dropped from the study. This allows us to exclude tests with sensitivities of 50%, 60%, 70%, or 80% after the first 50, 60, 80, and 120 participants recruited. For tests with poor specificities of 80%, 85%, 90%, or 95% these would be identified after 15, 20, 30, and 60 participants recruited. The prevalence of COVID-19 affects the sample size required. With a pre-test probability (prevalence) of 5% we would require 1200 participants to evaluate a POCT and interim futility analyses will stop the evaluation after seven false negatives or twelve false positives. POCTs with an actual sensitivity of 50%, 60%, 70%, or 80% would reach futility criteria after the first 280, 350, 470, and 700 participants. POCTs with an actual specificity of 80%, 85%, 90% or 95% would reach futility criteria after the first 65, 85, 130, and 255 recruited participants.

Evaluations of the first POCTs will be performed without implementation of stopping criteria to establish whether sufficient information to create the composite reference standard can be obtained sufficiently quickly to make these criteria viable. The figures presented here should therefore be regarded as indicative for a POCT designed to detect active infection and will be reviewed once this information becomes available.

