### Strengths and limitations

The prevalence of SARS-CoV-2 in the tested population will be the primary determinant of the rate at which RAPTOR-C19 can evaluate the accuracy of each POCT. The UK had surpassed a peak of SARS-CoV-2 infections at the time this protocol was being prepared for publication, with national easing of lockdown underway. COVID-19 testing capacity in the NHS took time to develop, with initial testing mainly occurring in the hospital setting, later through local COVID-19 ‘hubs’ and then national testing centres. At the height of the first peak, the prevalence of infection was > 30% in those tested [38]. As testing increased outside of the hospital setting, the prevalence of SARS-CoV-2 infections fell, due to a combination of decreasing national SARS-CoV-2 infection prevalence and increased testing in a broader population [39]. Whilst we welcome this reduction in prevalence, it results in larger sample sizes for clinical research.

By recruiting symptomatic people who are clinically suspected to have SARS-CoV2 infection, RAPTOR-C19 will increase the likelihood of identifying positive cases in the community above the background prevalence. To maximise recruitment RAPTOR-C19 will recruit from a base of high-throughput practices, with large practice populations, and/or practices acting as COVID-19 hubs, with wide geographical spread throughout the UK, including urban centres with high population density. Additional practices will be asked to act as stand-by sites where evaluation may begin rapidly in response to local outbreaks of SARS-CoV-2. This combined approach is intended to increase the likelihood of capturing positive cases in symptomatic people above the background national prevalence of SARS-CoV-2. From a public health point of view, correctly ruling-in active SARS-CoV-2 is just as important as ruling it out. Therefore, we need POCTs that are both highly sensitive and highly specific. The CONDOR triage process aims to identify POCTs that align with the MHRA specification based on the available data from the manufacturer or independent analytical analyses. By starting with a rigorous selection process, we reduce the probability of evaluating poorly performing POCTs.

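### Composite standard 1 for active infection counts infections acquired up to 28 days after the POCT as POCT misses, which biases enhanced sensitivity downwards, materially so at low prevalence

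*Protocol article*

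**What the plan says.** The section Composite reference standards (Table 4 and the interpretation below it) defines how composite standard 1, built to minimise false negatives, can overturn a negative baseline RT-PCR for current infection. There are three alternative routes:

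- Serology: "it can be considered a false negative if the IgG result is positive at 28 days (newly positive or titres have increased".
- A further RT-PCR that is positive within 28 days.
- "Hospital admission or death (within 28 days) citing SARS-CoV-2 as probable cause".

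All three run to day 28. None asks for a link between the later event and the illness that brought the participant to the baseline visit. Under Baseline assessments, the POCT is done at that first visit.

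On infection acquired in between, the protocol says that "infection could occur after the index test but prior to the day 28 serology sample, this is unlikely to be a frequent event". It offers no figure.

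Table 4 is captioned as potential and hypothetical. Even so, Summary statistics of diagnostic accuracy commits the enhanced 2 × 2 tables for active infection to "the composite reference standards as outlined in Table 4".

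Eligible participants include people with symptoms who have "lived or worked in close contact with somebody who has tested positive for SARS-CoV-2, including NHS staff", and Strengths and limitations plans "stand-by sites where evaluation may begin rapidly in response to local outbreaks of SARS-CoV-2".

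**The concern.** A test done on day 0 cannot detect an infection acquired on day 8. The rule places such a person in the infected row, where the day-0 POCT is almost always negative. Enhanced sensitivity therefore falls for a reason unrelated to the POCT.

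The protocol's defence is that such infections are infrequent. That is the wrong comparison. What counts is their number relative to the infected participants in the sensitivity denominator. When few of those tested are infected, a small fraction of a large uninfected group can be sizeable against a small infected group. The defence also covers only the serology route, although later RT-PCR results and admissions are accepted over the same 28 days.

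At stake is a secondary objective: accuracy for active infection against the enhanced standard. A fall in sensitivity from the RT-PCR comparison to composite 1 would mix two things, correct recovery of RT-PCR misses and wrongly counted later infections. The planned tables cannot separate them.

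**Working it through.** **Inputs from the protocol.** Stopping criteria gives a POCT with 90% sensitivity and 99% specificity, 200 participants at 30% prevalence, and "With a pre-test probability (prevalence) of 5% we would require 1200 participants to evaluate a POCT". Number of participants gives 80% as an example minimum sensitivity. Composite reference standards quotes RT-PCR false-negative rates of 18% to 58%.

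**Assumed input.** *i* is the 28-day risk, among those uninfected at baseline, of a new infection that also meets the rule. The protocol gives no value, so a range is shown.

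**Reproducing the plan's figures.** Infected participants: 200 × 0.30 = 60 and 1200 × 0.05 = 60. Expected recruitment to seven false negatives is 7 / [prevalence × (1 − sensitivity)]. For sensitivities of 50%, 60%, 70% and 80% this gives 46.7, 58.3, 77.8 and 116.7 at 30% prevalence, and 280, 350, 466.7 and 700 at 5%. These match the stated 50, 60, 80, 120 and 280, 350, 470, 700 after rounding up. The scenarios are therefore 60 infected with 140 uninfected, and 60 infected with 1140 uninfected (19 to 1).

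**Bias, ignoring RT-PCR misses.** Let n = *i* × uninfected. If the day-0 result is independent of later infection, only 1% of these people test positive, so

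apparent sensitivity = (0.9 × 60 + 0.01 n) / (60 + n).

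| Assumed *i* | n at 5% prevalence | Sensitivity | n at 30% prevalence | Sensitivity |
|---|---|---|---|---|
| 0 | 0 | 90.0% | 0 | 90.0% |
| 0.5% | 5.7 | 82.3% | 0.7 | 89.0% |
| 1% | 11.4 | 75.8% | 1.4 | 88.0% |
| 2% | 22.8 | 65.5% | 2.8 | 86.0% |

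Apparent sensitivity reaches 80% when 54 + 0.01 n = 0.8 (60 + n), so n = 6 / 0.79 = 7.59. That is 7.59 / 1140 = 0.67% incidence at 5% prevalence and 7.59 / 140 = 5.4% at 30%. Expected specificity stays at 99%.

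**Bias, allowing for RT-PCR misses.** Now take the 60 as RT-PCR positives among 1200, assume that composite 1 recovers every genuine miss, assume that the POCT detects 90% of all infected, and set *i* = 1%.

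- 18% false-negative rate: infected = 60 / 0.82 = 73.2, so 13.2 genuine misses. Uninfected = 1126.8 and n = 11.3. Sensitivity = (65.85 + 0.11) / (73.2 + 11.3) = 78.1%. Share of relabelled people wrongly relabelled = 11.3 / (11.3 + 13.2) = 46%.
- 58% false-negative rate: infected = 60 / 0.42 = 142.9, so 82.9 genuine misses. Uninfected = 1057.1 and n = 10.6. Sensitivity = (128.57 + 0.11) / (142.9 + 10.6) = 83.9%. Share wrongly relabelled = 10.6 / (10.6 + 82.9) = 11%.

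**False-negative count, if composite 1 fed the stopping rule.** At 5% prevalence and *i* = 1%, ignoring RT-PCR misses, expected false negatives rise from 6 to 6 + 0.99 × 11.4 = 17.3, against a limit of seven. By simulation (400,000 draws), the chance of more than seven rises from 25% to over 99%. At 30% prevalence it rises from 25% to 46%.

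**The case against.** The strongest reply is that the limitation is disclosed and bracketed. Composite 1 is deliberately inclusive and is reported beside composite 2 and the plain RT-PCR comparison. Table 4 is described as potential, the interpretation says only that a negative can be considered false, and patient-reported outcomes are among the listed ingredients, so the SAP, which is not shown here, may refine the rule. This limits the weight of the point but does not remove it. Composite 2 for current infection relabels only RT-PCR positives and so cannot identify later infections. The flat window and its justification are both stated in this document.

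The objections to size largely stand. A reader might infer more than the protocol supports:

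- *That sensitivity would fall to 65.5% to 82.3%.* Every incidence is assumed, and that calculation leaves out the RT-PCR misses the composite exists to recover. Pairing the lowest prevalence with outbreak-level exposure is also selective, because outbreak sites are meant to raise prevalence among those tested.
- *That about half of relabelled people are wrongly relabelled.* This holds only at 1% incidence with the lowest quoted RT-PCR false-negative rate. At the highest it is 11%.
- *That contacts are mostly infected later.* They qualify only with symptoms, so they may already be infected at baseline. The record search for household contacts is a fallback route.
- *That different POCTs become non-comparable.* Each is to be summarised independently, and no comparison between evaluations is described.
- *That the primary result or the stopping rule is compromised.* The primary comparison uses RT-PCR alone. Stopping criteria and Strengths and limitations link stopping to the composite without saying which one, and the first evaluations run without stopping.

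**Conclusion.** The point holds in direction. As written, composite 1 counts infections acquired after the day-0 POCT as infection present at baseline, so enhanced sensitivity for active infection is biased downwards. This rests on the POCT result being independent of later infection.

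The size is conditional. With 1% assumed incidence in the 5% scenario, apparent sensitivity is 75.8% if RT-PCR misses are ignored, and about 78% to 84% if false-negative rates of 18% to 58% apply and the POCT detects 90% of all infected. At 30% prevalence the loss at 1% to 2% incidence is 2 to 4 points. A low rate is therefore not enough to dismiss the problem at low prevalence, while at high prevalence it is minor. Correlated errors between POCT and RT-PCR would lower both the correct and the biased values.

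The effect is clear for one secondary analysis. It reaches stopping decisions only if composite 1 supplies the false-negative count.

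**What to change.** Keep the 28-day composite and pre-specify a timing-restricted version of composite 1 for current infection beside it:

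- Count a later positive RT-PCR or an admission or death only within a shorter window after baseline, with the length justified in the plan.
- Report separately, as timing uncertain, any relabelling that rests on day-28 serology alone or on an event outside that window. Use the symptom diary where it was completed.
- Show enhanced sensitivity under both versions, and over a range of window lengths and assumed post-baseline incidence.
- Replace the statement that post-index infection is unlikely to be frequent with this assessment.
- State that the unrestricted composite 1 will not supply false-negative counts for stopping.

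The cost is a further definition and some added tables, using the dates of RT-PCR results and admissions. No new visit is needed. The downside is that some genuine RT-PCR false negatives confirmed late will be classed as timing uncertain in the restricted version. The diary is optional and limited to adults, and the article describes no collection of exposure data after baseline, so timing will stay unresolved for some participants. Reporting both versions keeps that visible.

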### Statistical analysis

Results will be presented according to the Standards for Reporting Diagnostic accuracy studies (STARD) guidelines for reporting diagnostic studies.

### Descriptive analysis

Characteristics of recruited participants will be summarised using tables and graphs. If applicable, these will be compared to estimates from the general population. Number of total valid tests by POCT and reference standards will also be reported (actual and percentages), stratified by children vs adults and by age groups (if feasible dependent on total counts).

### Summary statistics of diagnostic accuracy

Sensitivity, specificity, and positive and negative predictive values for each POCT will be calculated with exact 95% confidence intervals.

For the primary outcome and first secondary outcome:

For consecutive POCTs for active infection, the diagnostic accuracy of each POCT will be summarised independently using 2 × 2 tables for POCT (+/-) and the current standard PHE reference test (+/-) for active infection. For consecutive POCTs for past infection, the diagnostic accuracy of each POCT will be summarised independently using 2 × 2 tables for POCT (+/-) and the current standard PHE reference test (+/-) for past infection. Measures of diagnostic accuracy will also be presented adjusted for imperfect reference standard bias, using the best available estimate of the accuracy of the PHE reference test.

For the second and third secondary outcomes:

For consecutive POCTs for active infection, the enhanced diagnostic accuracy of each POCT will be summarised independently using 2 × 2 tables for POCT (+/-) and the composite reference standards as outlined in Table 4 (+/-). For consecutive POCTs for past infection, the enhanced diagnostic accuracy of each POCT will be summarised independently using 2 × 2 tables for POCT (+/-) and the composite reference standards (+/-) for past infection.

Results for the primary outcome will be stratified by adults vs children, by age group (< 16, 16–40, 40–60, 60+ years), by gender, by ethnicity and by spectrum of disease (a combined measure of symptom severity and duration). A further subgroup analysis will test for differences in diagnostic performance by practice, and if any differences are detected, associations with practice size, location and model of care will be explored.

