In-context evaluation must reflect both the dynamics of disease transmission and the capabilities of those performing the test to be confident about the test performance in a particular setting. Most of the current data for analytical performance of new POCTs for SARS-CoV-2 is from small and selective patient samples tested within laboratories by highly trained staff [17–19]. Studies in clinical settings have focused on hospitalised patients who are more likely to have higher viral loads, and may undergo invasive procedures to increase yield of respiratory tract sampling [20]. Community settings are characteristically different, and extrapolating results from elsewhere risks spectrum bias and low confidence in results [21]. POCTs must work well when there is a lower prevalence and severity of disease, overlap in presentation with other common clinical syndromes, and in elderly and frail patients who may mount weaker immune responses [22]. Community staff performing POCTs have little-or-no laboratory experience and no ready access to technical support. False negatives are more damaging as ambulatory patients can potentially propel community transmission, whilst false positives in otherwise healthy individuals could hamper efforts to kickstart return to work and education [23].

We therefore aim to undertake context-specific evaluations of multiple POCTs, across a national network of community settings. Our platform design will allow for flexibility in which POCTs are evaluated, changes in Public Health England (PHE) choice of reference standard, and dynamics of local infection rates. RApid community Point-of-care Testing fOR COVID-19 (RAPTOR-C19) is the community testbed to the COVID-19 National DiagnOstic Research and Evaluation Platform (CONDOR) [24]. CONDOR co-ordinates evaluation of diagnostic performance of in vitro diagnostics, across laboratory, community, interface medicine, and secondary-care networks.

This document summarises the key points of the RAPTOR-C19 diagnostic study protocol.

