### Setting

RAPTOR-C19 sites will be community based. The primary community setting will be primary care, focussing on general practices reviewing patients with suspected COVID-19 or acting as COVID-19 hubs. Practices that have submitted an expression of interest to take part in the study will be selected with the help of the National Institute for Health Research (NIHR) Clinical Research Network (CRN). RAPTOR-C19 sites will be reimbursed per patient recruited for their participation in the research. Participants will not be paid for their participation in the research.

Practices will be initially recruited through Oxford Royal College of General Practitioners (RCGP) Clinical Informatics Digital Hub (ORCHID) [30]. The surveillance platform of ORCHID is called the Oxford-RCGP Research and Surveillance Centre (RSC). General practices within this network are experienced in taking virology samples and serology specimens and have adapted their long established influenza surveillance to provide a sentinel system for COVID-19, including sero-surveillance [31]. Additionally, they have also previously successfully integrated POCTs into primary care clinical workflow in the 2018/2019 flu season [32, 33] with an additional pilot conducted across the 2019/2020 season. Recruiting patients into RAPTOR-C19 is an integral part of the planned 2020/21 ORCHID/PHE surveillance [34]. Patients who volunteer to provide samples for surveillance will have the opportunity to take part in RAPTOR-C19 in participating practices, and samples taken, with consent through RAPTOR-C19, will also be available to use for national surveillance.

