### Illustrative sample sizes

Table 5 presents illustrative sample sizes to achieve a range of POCT sensitivities based on a standard error of 2.5%. A standard error of 2.5% will give a confidence interval of 5% on either side of the sensitivity estimate.

**Table 5 Tab5:** Illustrative sample sizes to achieve a range of POCT sensitivities based on a standard error of 2.5%

	Prevalence	40%	35%	30%	25%	20%	15%	10%	5%
**Sensitivity**	**95%**	190	218	254	304	380	507	760	1520
	**90%**	360	412	480	576	720	960	1440	2880
	**85%**	510	583	680	816	1020	1360	2040	4080
	**80%**	640	732	854	1024	1280	1707	2560	5120
	**75%**	750	858	1000	1200	1500	2000	3000	6000
	**70%**	840	960	1120	1344	1680	2240	3360	6720

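### The exact intervals and Table 5 treat participants as independent, so they overstate precision if accuracy varies by practice and practices are few or large

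*Protocol article*

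**What the plan says.** All places are in the protocol article. Its statistical analysis plan is not at hand.

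- Summary statistics of diagnostic accuracy, on the interval: "Sensitivity, specificity, and positive and negative predictive values for each POCT will be calculated with exact 95% confidence intervals".
- The same section, on the table behind it: "the diagnostic accuracy of each POCT will be summarised independently using 2 × 2 tables for POCT (+/-) and the current standard PHE reference test". It names no practice term and no clustered variance.
- The same section, on practice: "A further subgroup analysis will test for differences in diagnostic performance by practice". If differences appear, the planned response is to explore practice size, location and model of care. Nothing says that the main intervals would change.
- Illustrative sample sizes: "A standard error of 2.5% will give a confidence interval of 5% on either side of the sensitivity estimate".
- Setting: "The primary community setting will be primary care, focussing on general practices reviewing patients with suspected COVID-19 or acting as COVID-19 hubs".
- Background, on the operators: "Community staff performing POCTs have little-or-no laboratory experience and no ready access to technical support".
- Strengths and limitations: recruitment favours high-throughput practices and hubs, and "Additional practices will be asked to act as stand-by sites where evaluation may begin rapidly in response to local outbreaks of SARS-CoV-2".
- Number of participants: 80% sensitivity and 95% specificity are given as example minimum thresholds.

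**The concern.** The participant is the unit of measurement, but participants reach the study through practices, whose staff assist with or observe the test. The Background section says that test performance in a setting depends on the capabilities of the people performing the test. If those differ between practices, two participants from one practice share part of their chance of a correct result, and the pooled table carries less information than its count suggests. An exact binomial interval cannot see this.

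The interval is what a reader will compare with the 80% and 95% thresholds. If it under-covers, a test whose true accuracy lies at a threshold will be shown as above it more often than the nominal 2.5%. The plan also leaves an internal gap: its own subgroup test could show that the independence assumption has failed, and the headline intervals would still be reported unchanged.

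**Working it through.** **1. Reproduce Table 5.** With sensitivity p, cases = p(1 − p)/0.025² and N = cases/prevalence. At p = 0.90, 0.09/0.000625 = 144 cases, so N = 144/0.30 = 480 and 144/0.10 = 1440, as printed. All 48 cells reproduce to rounding. The table is therefore the simple binomial calculation, with no design effect.

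**2. Inputs the documents do not give.** The number of practices K, their sizes and the ICC (ρ) are assumed: K from 10 to 80, ρ from 0.01 to 0.10, and practice sizes with a coefficient of variation of 0.65.

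**3. Standard error of sensitivity, n = 144 cases, p = 0.90.** Design effect = 1 + (n − 1) × ρ × Σw², where w is each practice's share of cases. For gamma-distributed sizes, a = 1/0.65² = 2.367 and the expected Σw² = (a + 1)/(Ka + 1). The standard error is 2.5 × √(design effect). For K = 10 and ρ = 0.05: Σw² = 3.367/24.67 = 0.1365; design effect = 1 + 143 × 0.05 × 0.1365 = 1.98; standard error = 3.5.

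| Practices | Σw² | SE, ρ = 0.01 | SE, ρ = 0.05 | SE, ρ = 0.10 | Simulated exact coverage, ρ = 0.05 |
|---|---|---|---|---|---|
| 10 | 0.137 | 2.7 | 3.5 | 4.3 | about 86% |
| 20 | 0.070 | 2.6 | 3.1 | 3.5 | about 91% |
| 40 | 0.035 | 2.6 | 2.8 | 3.1 | about 94% |
| 80 | 0.018 | 2.5 | 2.6 to 2.7 | 2.8 | about 96% |

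The last column comes from beta-binomial simulation, which gives standard errors of 3.5, 3.1, 2.8 and 2.6 at ρ = 0.05. With no variation in accuracy, coverage is 96 to 97%, because the exact interval is conservative. That reserve is why coverage stays at about 95 to 96% at ρ = 0.01.

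**4. Same check with equal practice sizes** (480 participants, prevalence 30%):

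| Practices | SE, ρ = 0.05 | Coverage | SE, ρ = 0.10 | Coverage |
|---|---|---|---|---|
| 12 of 40 | 3.17 | 90.7% | 3.70 | 84.7% |
| 24 of 20 | 2.85 | 93.5% | 3.14 | 90.7% |
| 48 of 10 | 2.65 | 95.3% | 2.81 | 93.8% |

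**5. Specificity.** There are more non-cases per practice, so the effect is larger. With 480 − 144 = 336 non-cases, equal sizes and ρ = 0.05, the design effect 1 + (m − 1)ρ is 1 + 32.6 × 0.05 = 2.63 for 10 practices and 1 + 15.8 × 0.05 = 1.79 for 20. At a true specificity of exactly 95%, simulated coverage is 82.0%, 89.4% and 93.3% with 10, 20 and 40 practices. The lower limit wrongly exceeds 95% in 8.3%, 4.6%, 2.8% and 2.1% of evaluations with 10, 20, 40 and 80 practices. At ρ = 0.01 and equal sizes it does so in 2.5% or fewer for every practice count.

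**6. Prevalence varying, accuracy constant.** Sensitivity conditions on being a case. With prevalence ICC 0.05 to 0.10 and 12, 24 or 48 practices, its standard error stays at 2.49 to 2.53 and coverage at about 96.5%. Predictive values can move: at prevalence ICC 0.10, negative predictive value coverage is 91%, 93.5% and 95% with 12, 24 and 48 practices, while positive predictive value coverage stays near 97 to 98%.

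**The case against.** The strongest reply is that the size of the effect rests on inputs that the documents do not contain. The article describes a national network with wide geographical spread, so 10 practices is not a documented scenario. With 40 to 80 practices, or an ICC of 0.01, the exact interval for sensitivity covers 94 to 96%. This stands, and it makes the point conditional. The same section of the article also favours high-throughput practices and hubs, so few large practices cannot be ruled out either.

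Practice is not ignored. A test for differences is planned, training is organised centrally, and photographs of qualitative results are adjudicated by blinded independent staff. It would therefore be wrong to infer that results are read only within practices. Central adjudication limits variation in reading, but not in sampling, operation or case mix, and the planned test does not feed back into the intervals.

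A reader might infer that prevalence differences, for instance from outbreak stand-by sites, also break Table 5. They do not (step 6). For predictive values the answer depends on scenario and target. With practice prevalence spread uniformly over 5 to 40%, sensitivity 80%, specificity 95% and N = 1020, negative predictive value coverage is 76% and 85% with 10 and 20 practices. At 90% and 99% with N = 640 it is 92% and 94%. If the target is the prevalence of the included practices themselves, coverage is 96% or more.

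Finally, Table 5 is labelled illustrative, and the analysis plan may contain a clustered interval. Both are true. The article nevertheless names the simple exact interval as the analysis.

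**Conclusion.** The point holds in conditional form. The article fixes an interval and a planning standard error that are right only if sensitivity and specificity do not vary between practices, while its own text treats such variation as plausible enough to test. Under an assumed ICC of 0.05 and unequal practices, coverage for sensitivity 90% with 144 cases runs from about 86% with 10 practices to about 96% with 80, and specificity is affected more. At an ICC of 0.01, or with many small practices, there is little or nothing to correct.

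Three stronger readings are not supported: that the 95% intervals are too narrow as a matter of fact, that varying prevalence alone invalidates the 2.5% standard error, and that Table 5 misstates a required sample size. This is a worthwhile, low-cost improvement and not a demonstrated error in the results to come.

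**What to change.** In Summary statistics of diagnostic accuracy, keep the exact interval and pre-specify a practice-clustered interval beside it for each accuracy measure. One option is Korn-Graubard with practice as the cluster: a Clopper-Pearson interval on the effective sample size from the between-practice variance, with a t correction on practices minus one and the effective size capped at the actual n. Base any statement that a test meets the minimum thresholds on the wider of the two intervals. For predictive values, state the population to which they refer.

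In Illustrative sample sizes, say that Table 5's 2.5% assumes no between-practice variation in accuracy, and show the standard error over a range of assumed design effects, for example 2.5 × √1.5 = 3.1 and 2.5 × √2 = 3.5.

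The cost is wording and a few lines of code. Practice must already be identifiable for the planned subgroup test, and no extra participants are needed. The downside is sensitivity intervals about 0.4 points (80 practices) to 1.7 points (10 practices) wider if there is no clustering, against about 10.4 points for the exact interval. The clustered interval restores coverage for sensitivity to about 94 to 97% at ICC 0.05, but corrects only partly for high specificity in few practices.
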